## Abstract

Migori County is located in western Kenya bordering Lake Victoria and has traditionally performed poorly on important health metrics, including child mortality and HIV prevalence. The Lwala Community Alliance is a non-governmental organization that serves to promote the health and well-being of communities in Migori County through an innovative model utilizing community health workers, community committees, and high-quality facility-based care. This has led to improved outcomes in areas served, including improvements in childhood mortality. As the Lwala Community Alliance expands to new programming areas, it has partnered with multiple academic institutions to rigorously evaluate outcomes. We describe a repeated cross-sectional survey study to evaluate key health metrics in both areas served by the Lwala Community Alliance and comparison areas. This will allow for longitudinal evaluation of changes in metrics over time. Surveys will be administered by trained enumerators on a tablet-based platform to maintain high data quality.

## Introduction

Migori County is located in western Kenya bordering Lake Victoria (Fig 1). One of the 47 counties in Kenya, Migori has historically underperformed on many important health metrics. For example, the under-five mortality rate in 2014 was 82 per 1,000 live births compared with 52 per 1,000 live births for Kenya as a whole [1]. HIV prevalence as of 2018 was 13% in Migori County compared to 4.9% nationally [2]. Per the 2014 Kenya Demographic Health Survey (DHS), only 57.2% of children in Migori County were fully vaccinated compared with 74.9% for Kenya as a whole [1]. Importantly, most data on these health indices come from national surveys such as the DHS and are disaggregated only to the regional or county level. Hyper-local data to inform programming efforts in smaller areas is frequently not available.

**Fig 1 pone.0256555.g001:**
[figure not shown]
Migori County, Kenya. Lwala programming began in North Kamagambo in Rongo sub-county (green). By 2021, programming will include all of Rongo sub-county. The next expansion is planned for Awendo (orange). Two areas in Uriri, Central Kanyamkago and West Kanyamkago, serve as comparison wards (red).

The Lwala Community Alliance (Lwala) is a non-governmental organization that serves to promote the health and well-being of communities in the Rongo sub-county of Migori County, Kenya (Fig 2). Founded in 2007, Lwala initially worked in the community of North Kamagambo ward of Rongo sub-county with services including the operation of a hospital and clinic with inpatient, outpatient, maternal, and HIV care, as well as an innovative Community Health Worker (CHW) program incorporating traditional birth attendants. The CHW program is distinguished by its consistent payment, supportive supervision, and proactive community case finding and case management. This community health worker structure is supported by community committees that plan health initiatives and advocate for child rights, reproductive rights, sanitation infrastructure, and reduced HIV stigma.

**Fig 2 pone.0256555.g002:**
[figure not shown]
Lwala Community Alliance theory of change. Lwala utilizes a community-led model to improve health, education, and economic outcomes.

Lwala’s efforts in North Kamagambo have led to significant successes in several key health metrics, including being on track to outpace Millennium and Sustainable Development Goal (SDG) targets for childhood mortality, attaining an under-five mortality rate of 29.5 per 1,000 live births as of 2017 [3] compared to the SDG target of under 25 deaths per 1,000 live births by 2030 [4]. This success has led to local health authorities inviting Lwala to expand its CHW model into nearby East and South Kamagambo wards, as well as to begin providing technical assistance toward improved health service delivery in the government-supported health facilities of these wards. Along with service expansion has come the effort to systematically and academically evaluate health metrics and changes in outcomes in the community. This led to multiple iterations of a community-wide household survey in Lwala’s original catchment area and subsequently in the expansion areas [3,5,6]. We now aim to conduct repeated cross-sectional surveys to evaluate the effect of Lwala’s programming over time and characterize health metrics in the area.

Here we describe the Lwala Household Survey (LHS) with the following objectives: (1) to assess the health, socioeconomic, and education status of current and future communities receiving programming from Lwala; (2) to measure changes in these metrics over time in the presence of Lwala programming; (3) to compare changes over time in key metrics to determine the effect of Lwala presence and programming.

## Methods

### Study design

This is a repeated, cross-sectional survey allowing for longitudinal analyses of population and community-level metrics related to health, education, and socioeconomics. Households will be selected for surveying in areas currently receiving Lwala programming and in areas planned to receive Lwala programming in the future. Nearby geographic regions with no planned Lwala services will be surveyed and serve as comparison locations. Subsequent surveys will provide new cross-sectional data for a given geographic area by randomly selecting households for interview utilizing the same sampling strategy; however, it will not specifically target the same households for future surveying. Data collection will begin in 2021 and occur every three years until 2027. Previous surveys have been conducted in 2017 and 2019.

### Study population, setting, and timeline

Located in the Lake Victoria region of southwestern Kenya, Migori county had a population of 1.1 million people during the 2019 National Census [7]. Administratively, there are 10 sub-counties, each with multiple smaller electoral sub-divisions called wards [8]. With an average household size of 4.6 and a growth rate of 3.1%, it is highly densely populated (427 persons per square kilometer) [7,8]. About 90% of the population live in rural areas, largely in mud-walled houses with agriculture and fishing as the main livelihoods [8].

Lwala programming began in North Kamagambo, an area covering 46.4 square kilometers, in Rongo, which is one of the 10 sub-counties, in 2007 (Fig 1). Programs were subsequently expanded to other wards in Rongo, namely East Kamagambo in 2018 and South Kamagambo in 2019. Programming will be expanded to Central Kamagambo within Rongo in 2021 following the first survey administration. Lwala’s area of programming is expanding approximately every two years, with the next round of expansions planned for Awendo sub-county. The first iteration of this survey in 2021 will be administered in current programming wards in Rongo sub-county (North Kamagambo, East Kamagambo, South Kamagambo) and the future programming ward in Rongo sub-county (Central Kamagambo). It will also include two representative wards in Awendo sub-county (North Sakwa and Central Sakwa).

The initial survey will also include two comparison wards in Uriri sub-county (Central Kanyamkago and West Kanyamkago). Uriri sub-county is adjacent enough to be a comparable location but distant enough to minimize spillover effects. In addition, Uriri sub-county has a similar socio-economic and demographic context that is analogous to Rongo sub-County. Within Uriri sub-County, Central Kanyamkago was selected as a peri-urban ward to serve as a comparison with the peri-urban Central Kamagambo. Similarly, West Kanyamkago was selected as a rural ward to compare with more rural programming wards. While Uriri has government health facilities that are typical of Migori County, there is no similar organization to Lwala.

All subsequent surveys (2024 and 2027) will include the areas from the initial 2021 survey (Table 1). Any further expansion areas that are identified will also be included. Inclusion of new wards will be approved by the investigators with subsequent amendments made to Institutional Review Board protocols.

**Table 1 pone.0256555.t001:** Survey timepoints across areas.

Sub-County	Ward	Intervention	2017*	2019*	2021	2024	2027
Rongo	North Kamagambo	2007	X	X	X	X	X
	East Kamagambo	2018		X	X	X	X
	South Kamagambo	2019		X	X	X	X
	Central Kamagambo	2021		X	X	X	X
Awendo	North Sakwa	2022			X	X	X
	Central Sakwa	2022			X	X	X
Uriri	Central Kanyamkago	Comparison		X	X	X	X
	West Kanyamkago	Comparison		X	X	X	X

*Surveys conducted as a part of previous works.

### Sample size

The study has a wide range of indicators of interest, including child mortality, skilled delivery rate, vaccination coverage, contraceptive prevalence, and antenatal care. These metrics vary in their community prevalence and would thus require different sample sizes. For example, under-five mortality is relatively rare at 82 per 1,000 live births while full vaccination is relatively common at 57.2% of children [1]. A community prevalence of 50%, yielding maximum variation and therefore maximum sample size, was used to adequately power all metrics. Within each area, the sample size was calculated to detect a 10% difference over time using a power of 80%, precision of 0.05, and design effect of 1.6. Design effect was calculated according to the equation:
DE=(1+(m−1))*ICC
where DE is the design effect, m is the number of the household to be sampled per cluster, and ICC is the inter-cluster correlation. An ICC of 0.15 was used based on international standards [9]. This would require a sample of 621 households in each area. This estimate was inflated by 30% to give a total goal sample of 887 per area. For the first survey, which includes eight areas, the total sample size will be 7,096 households. Subsequent surveys will include the same number of households per area. Table 2 below shows the sample size for each ward.

**Table 2 pone.0256555.t002:** Sample sizes for successive surveys.

	Minimum	Maximum	Number of clusters	Households with children	Additional Households	Total per Cluster
North Kamagambo	621	887	127	5	2	7
East Kamagambo	621	887	127	5	2	7
Central Kamagambo	621	887	127	5	2	7
South Kamagambo	621	887	127	5	2	7
North Sakwa	621	887	127	5	2	7
Central Sakwa	621	887	127	5	2	7
Central Kanyamkago	621	887	127	5	2	7
West Kanyamkago	621	887	127	5	2	7

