### Data analysis

After administration, data will be exported to the latest version of Stata (StataCorp LP, College Station, TX) for further analysis. Initial analyses will focus on descriptive statistics of health, socioeconomic, and education metrics in the sample population across areas. Further analyses will characterize these metrics in terms of demographic variables and compare these metrics to county and national averages using appropriate statistical tests, including chi-squared tests, t-tests, ANOVA, and non-parametric tests. These analyses will be conducted following each survey in 2021, 2024, and 2027.

Analysis of outcome metrics will be conducted using multivariable linear regression, logistic regression, and generalized estimating equations. Specific primary outcomes of interest include under-five mortality, immunization rate, skilled delivery rate, contraceptive prevalence rate, and antenatal care visits. Longitudinal analyses will be performed at the end of the study in 2027 once multiple timepoints are available. Interim longitudinal analyses will also be performed following each survey administration. Trends in outcomes and potential effects of programs will be assessed. This will involve interrupted time series techniques with a segmented regression to asses intervention effects over repeated observations.

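### The 50%-prevalence, 10-point calculation does not power under-five mortality, although the plan says that it powers every metric

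*Protocol article*

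**What the plan says.** The Sample size section of the protocol article notes that the indicators differ in how common they are and so would need different sample sizes. Its own example of a rare one is that "under-five mortality is relatively rare at 82 per 1,000 live births". It then settles on one calculation for everything: "A community prevalence of 50%, yielding maximum variation and therefore maximum sample size, was used to adequately power all metrics". The other inputs, applied to every ward separately, are given as follows: "the sample size was calculated to detect a 10% difference over time using a power of 80%, precision of 0.05, and design effect of 1.6". The results are: "This would require a sample of 621 households in each area" and "This estimate was inflated by 30% to give a total goal sample of 887 per area".

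The Data analysis section names the outcomes: "Specific primary outcomes of interest include under-five mortality, immunization rate, skilled delivery rate, contraceptive prevalence rate, and antenatal care visits". Table 3 (Survey instrument) shows that child mortality is taken from birth histories.

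**The concern.** A prevalence of 50% gives the largest sample size only if the absolute difference to be detected is the same for every metric. That cannot hold for an outcome at 8.2%, where any fall is necessarily smaller than 10 points. Smaller absolute differences at low prevalence can need more observations than the 50% calculation supplies. The claim of adequate power for every metric would then be wrong for the first outcome in the primary list.

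The stake is interpretation. If one ward shows no clear change in child mortality, a reader who trusts the statement may take this as adequately powered evidence of no effect, when power for a moderate fall may have been low.

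**Working it through.** **Inputs.** From Sample size: prevalence 50%, difference 10%, power 80%, 0.05 (printed as precision, read here as the significance level), design effect 1.6, 621 and 887 households, under-five mortality 82 per 1,000. From the Introduction: national under-five mortality 52 per 1,000, and 29.5 per 1,000 reached in North Kamagambo by 2017. From Sampling strategy and Table 2: 127 grid cells per area, with at least 5 of 7 surveys per cell in households with a child under five.

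**Step 1: reproduce the plan's figure.** For two independent proportions,

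n = [1.96·√(2p̄(1−p̄)) + 0.8416·√(p₁(1−p₁) + p₂(1−p₂))]² / (p₁−p₂)²

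With p₁ = 0.50, p₂ = 0.60, p̄ = 0.55:
- numerator = (1.96·√0.495 + 0.8416·√0.49)² = (1.379 + 0.589)² ≈ 3.873
- n = 3.873 / 0.01 = 387.3, rounded up to 388
- 388 × 1.6 = 620.8, rounded up to **621**
- 621 / 0.7 = 887.1, stated as **887**; 887 × 8 = 7,096

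The figures therefore reproduce with a two-sided 5% test and an absolute 10-point difference. Other readings do not fit: a 10% relative difference (50% to 55% or 45%) gives 2,504, a one-sided test gives 488, and a continuity correction gives 653.

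**Step 2: is 50% the worst case?** With the difference fixed at 10 points it nearly is: the maximum over all baselines is 392 per survey before the design effect, against 388. This holds only for that fixed difference.

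**Step 3: apply the planned effect to under-five mortality.** 8.2% − 10 points = −1.8%, which is impossible.

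**Step 4: births needed for falls that are possible.** The same formula for 82 to 52 per 1,000 (p̄ = 0.067):
- numerator = (1.96·√0.12502 + 0.8416·√0.12457)² = (0.6930 + 0.2970)² ≈ 0.980
- n = 0.980 / 0.0009 ≈ 1,089, rounded up to **1,090** effective births per survey, about 2.8 times the 388 behind the household figure (1,090 / 388)

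Likewise, a 25% fall (to 61.5) needs 2,487, a halving (to 41) needs 538, and a fall to 29.5 needs 299.

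**Step 5: power over a range of births.** The article gives neither births per household nor a design effect for births, so both are assumptions here. The rows take 621, 887 or 1,774 births per area per survey (1,774 being two per household at 887) and design effects of 1.6 and 1.0. Effective births are births divided by the design effect.

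| Births / design effect | Effective births | 82→61.5 (25% fall) | 82→52 | 82→41 | 82→29.5 | Fall detectable with 80% power |
|---|---|---|---|---|---|---|
| 621 / 1.6 | 388 | 20% | 39% | 66% | 89% | 57% |
| 887 / 1.6 | 554 | 26% | 52% | 81% | 97% | 49% |
| 621 / 1.0 | 621 | 29% | 56% | 85% | 98% | 47% |
| 887 / 1.0 | 887 | 39% | 72% | 95% | >99% | 40% |
| 1,774 / 1.6 | 1,109 | 46% | 81% | 98% | >99% | 36% |
| 1,774 / 1.0 | 1,774 | 66% | 95% | >99% | >99% | 29% |

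**Step 6: coverage metrics in households with a young child.** The quota gives 127 × 5 = 635 such households per area. At design effect 1.6, power for 50% to 60% is 80.9%.

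**The case against.** The best defence is that the arithmetic is sound for what it covers. The figures 621, 887 and 7,096 all reproduce, and for coverage metrics of moderate prevalence the claim is fair. The section itself acknowledges that metrics differ in the sample they need. Birth histories can yield several births per respondent, so the number of births may well exceed the number of households. With two births per household at the full target, a fall to the national rate has 81% to 95% power. A fall as large as the level already reported for North Kamagambo is detectable even at the lowest birth count considered. All of this stands. It limits the size of the problem but does not rescue a statement about every metric, because the effect on which that statement rests cannot occur as a fall in mortality.

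A reader might go further in three ways that the document does not support.

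- **Child metrics generally fall short.** Taking 5/7 of 621 gives about 444 households with a young child. But the quota applies to completed surveys in each grid cell, and enumerators continue until it is met. That gives 635 households, above the 621 required. The lower count arises only if the 30% allowance is lost evenly across household types.
- **Vaccination is underpowered because it uses one age cohort.** The article states no age window for vaccination, so no such denominator can be derived from it.
- **A ward can show only a halving of mortality or more.** This treats the household effective sample of 388 as a count of births. Over the range above, the detectable fall runs from about 57% down to 29%.

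**Conclusion.** The concern holds for under-five mortality. The claim of adequate power for all metrics is wrong for a listed primary outcome: the planned 10-point effect is impossible as a fall from 82 per 1,000, and the 50% worst case does not carry over to smaller differences at low prevalence. That conclusion rests only on the document's own figures.

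The size of the shortfall rests on assumptions: 388 to 1,774 effective births per area per survey, a simple comparison of two surveys within one area, and a two-sided 5% test. On that basis power is 39% to 95% for a fall to 52 per 1,000 and 20% to 66% for a 25% fall, but at least 89% for a fall to 29.5. Mortality is therefore not underpowered for every effect. Power for moderate falls is low or unknown until the number of births is stated. No shortfall is shown for coverage metrics measured once per household with a young child if the quota is met.

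**What to change.** In Sample size, delete the clause claiming adequate power for all metrics. Say instead that the design has 80% power for an absolute 10-point difference in coverage or prevalence metrics measured once per household, or once per household with a child under five (where the quota of 635 gives about 81%). Add one line for under-five mortality giving the detectable difference per ward, based on the expected number of live births per survey and a design effect suited to births, with both assumptions stated.

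The cost is one reworded sentence and one added line. No households, procedures or analyses change. The stated power for mortality becomes less favourable.

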### Sampling strategy

Households will be selected using a hybrid sampling technique to obtain as random of a sample as is feasible. Because a truly random sample would be logistically infeasible due to expense and lack of a household-level sampling frame, a hybrid systematic and random sampling technique will be used. To accomplish this, a modified procedure based on the World Health Organization Expanded Programme of Immunization (EPI) method will be used [10,11]. First, each area will be split into 127 grid squares using Geographic Information System (GIS) technology. The center point of each grid cell will then be generated using GIS. This is the starting location for the enumerators for each day’s survey. GPS will be used to navigate to the precise starting location each morning.

After arrival at the center point, the spin-the-bottle technique will be used [10]. Each enumerator team will be supplied with a random direction by spinning a pen or bottle. On arrival to the center of the grid cell, they will travel in the given direction surveying houses along the line given by the direction.

As many of Lwala’s programs and outcomes of interest focus around maternal and child health, households with children under five years of age will be oversampled. At least five of seven surveys administered in each grid square will be administered to households with children under five years. If the enumerator reaches the end of the grid cell before surveying both seven total households and five households with a child under five years, they will walk along the edge of the grid to the closest corner to find more households.

This approach minimizes the biases of the traditional spin-the-bottle sampling method [12] by using the center of an arbitrary square in place of the center of a town or gathering area.

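### The printed design-effect formula cannot give 1.6, and 1.6 implies 5 households per cluster where the plan samples 7, so the 621 minimum holds only for clusters of about 5.

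*Protocol article*

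**What the plan says.** The Sample size section takes a prevalence of 50% as the most demanding case: "A community prevalence of 50%, yielding maximum variation and therefore maximum sample size, was used to adequately power all metrics". The target is a change between survey rounds in a single area: "the sample size was calculated to detect a 10% difference over time". The remaining inputs are listed together: "using a power of 80%, precision of 0.05, and design effect of 1.6".

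The design effect is said to come from a printed equation, DE = (1+(m−1))*ICC. There "m is the number of the household to be sampled per cluster", and the ICC is set at 0.15. The result is then given: "This would require a sample of 621 households in each area". This is inflated by 30% to a goal of 887 per area.

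For every ward, Table 2 lists 621 as the minimum, 887 as the maximum, 127 clusters, and 5 households with children plus 2 additional households, a total of 7 per cluster. The Sampling strategy has the same rule: an enumerator who reaches the end of a cell "before surveying both seven total households and five households with a child under five years" goes on looking for more. The value of m behind 1.6 is not stated anywhere.

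**The concern.** Two things do not fit together. First, the bracket is in the wrong place: as printed, the ones cancel and the expression is m × ICC, which is not a design effect and does not give the value the section attributes to it. Second, the value used matches a cluster of 5, whereas m is defined as the households sampled per cluster and the plan samples 7.

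At stake is the meaning of the 621 floor in Table 2. A reader will take it as the number of households at which any area still has 80% power for a 10-point change in any metric. Whether that is true depends on how many households sit in each cluster, and the article does not say so.

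**Working it through.** **Inputs** (Sample size section unless noted)
- Prevalence 0.50; change of 10%, read as 10 percentage points, so 0.50 v 0.60, between two independent survey rounds in one area.
- Power 80%. The "precision of 0.05" is read as the significance level. Two-sided testing is an assumption, because sidedness is not stated.
- ICC 0.15; stated "design effect of 1.6".
- 127 clusters of 7 households, at least 5 of them with a child under five (Table 2; Sampling strategy).

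**1. Reproducing 621**

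n = [1.96 × √(2 × 0.55 × 0.45) + 0.8416 × √(0.25 + 0.24)]² / 0.10²
= (1.379 + 0.589)² / 0.01 = 387.3, rounded up to 388 per round.

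388 × 1.6 = 620.8, rounded up to 621. The plan's figure is reproduced.

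Other readings miss it: one-sided gives 488, unpooled variance 616, continuity-corrected 653, and 0.45 v 0.55 gives 628. A change to 0.55 (10% relative) gives 2,504.

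**2. Which m gives 1.6?**

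| Form | m = 5 | m = 7 |
|---|---|---|
| As printed: (1+(m−1)) × 0.15 = m × 0.15 | 0.75 | 1.05 |
| Standard: 1+(m−1) × 0.15 | 1.60 | 1.90 |

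The misprint did not enter the calculation, since 621 follows from 1.6 and 1.6 follows from the standard form at m = 5.

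**3. Minimum at 7 per cluster**

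388 × 1.9 = 737.2, rounded up to 738 households per area.

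**4. Power**

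Power = Φ{[0.10 × √(N/DE) − 1.379] / 0.70}

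| Households N | Layout | DE | N/DE | Power |
|---|---|---|---|---|
| 621 | as the plan assumes (m = 5) | 1.60 | 388.1 | 80.1% |
| 621 | full clusters of 7 (621/7 ≈ 89 cells) | 1.90 | 326.8 | 73.0% |
| 621 | even over 127 cells (4.89 each) | 1.58 | 392.2 | 80.5% |
| 621 | random 30% loss within cells | 1.63 | 381 | about 79% |
| 635 | 5 under-five households × 127 | 1.60 | 396.9 | 80.9% |
| 887 | the goal, clusters of 7 | 1.90 | 466.8 | 86.8% |

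For random loss, cell size is taken as binomial (7, 0.70), so CV² = (7 × 0.7 × 0.3)/4.9² ≈ 0.06 and DE = 1 + (4.89 × 1.06 − 1) × 0.15 ≈ 1.63. If cell sizes vary more, with CV² = 0.2, DE is about 1.73 and power about 77%.

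**5. Loss that 887 can absorb**

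The plan's allowance is 1 − 621/887 = 30%. With full clusters of 7 it is 1 − 738/887 = 16.8%, about 17%.

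**The case against.** The strongest reply is that the 73% describes a survey the protocol does not plan. Every area is divided into 127 cells, and 621 is what remains of 887 after a 30% loss. Spread over 127 cells that leaves about 4.9 households per cell, a design effect near 1.6 and power of 79–80%. With 127 clusters fixed and even loss, solving n = 388 × [1 + (n/127 − 1) × 0.15] gives about 609, which 621 exceeds. This stands, and it limits the point: 73% applies only if the shortfall takes the form of about 38 cells not worked. That pattern is possible, because the field rules replace absent households and keep the enumerator walking until seven are surveyed. The article does not say how a shortfall would arise.

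A second reply is that m = 5 was meant for households with young children, since most of the metrics named concern mothers and children. That is plausible, and 5 × 127 = 635 does exceed 621. But the text does not say it, the calculation is offered for all metrics, and contraceptive prevalence, a primary outcome, is not confined to those households. On this reading the guaranteed 635 also leaves only about 2% above 621 (635/621 = 1.02), so the 30% allowance would be made up of the two additional households per cell.

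A reader might go further and infer that the survey is underpowered, or that the goal must rise to 738/0.70, about 1,055. The documents do not support either. The goal of 887 has about 87% power at design effect 1.9, and losses within cells lower the design effect. Nor do they support a claim that the 2024 and 2027 rounds will be undersized by the misprint, because the section keeps the same number of households per area in later surveys.

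**Conclusion.** The point holds as an error in the stated basis of the sample size. The printed equation cannot produce the design effect attributed to it, and the value used belongs to clusters of 5 while the plan defines and samples clusters of 7. At 7 per cluster the design effect is 1.9 and the 80% minimum is 738, which is 19% above 621 (738/621 = 1.19). The published 621 is right only for about 5 households per cluster across all 127 clusters, or for under-five households.

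The planned sample itself is not put in doubt for the 50% v 60% scenario. What shrinks is the margin: about 17% loss with full clusters, where the plan implies 30%.

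This rests on a two-sided 5% test with pooled variance, an absolute 10-point change and the stated ICC of 0.15. The bracket error is taken from the article text as supplied and should be confirmed against the typeset page. The mismatch between m = 5 and 7 does not depend on it.

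**What to change.** In the Sample size section:
- Print DE = 1+(m−1)×ICC and state the value of m used.
- Give DE = 1.9 for metrics measured in all households at 7 per cluster, and DE = 1.6 for metrics limited to the five under-five households per cluster.
- Report that the goal of 887 gives about 87% power for 50% v 60% at DE 1.9.

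In Table 2, do one of two things: restate the minimum as 738 for full clusters of 7, or keep 621 with a note that it holds only for about 5 households per cluster across all 127 clusters, or for under-five households.

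The cost is a correction to the text and one table. No extra households are needed, since 887 already exceeds 738.
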